##### ART Adherence

The capacity to maintain ART regimens will be assessed using a novel single-item visual analog scale (VAS) [72]. The VAS asks participants to estimate the percentage of their medication that they have taken in the past 30 days. Details of the VAS format and development are provided by Giordano et al [121]. In addition, daily diary measures operationalizing use of and feelings toward ART medication will be administered over the 21-day trial period (eg, “Did you have difficulty fitting your HIV treatment into your daily routine yesterday [Yes/No]”). These measures are provided in full in Multimedia Appendix 3.

##### Viral Suppression

Virologic control will be assessed via a self-report item asking participants whether their most recent HIV viral load test result was <50 copies/mL at the 90-day follow-up assessment. This item is adapted from the study by Carter et al [122].

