**Methods:**

The development of NOLA GEM entailed identifying real-time tailoring variables via a geographic ecological momentary assessment (GEMA) study (n=49; aim 1) and place-based and user-centered tailoring, responsive to the unique cultural contexts of HIV survivorship in New Orleans, via formative interviews (n=12; aim 2). The iOS- and Android-enabled NOLA GEM app leverages twice-daily GEMA prompts to offer just-in-time, in-app recommendations for effective coping skills practice and app-delivered *Living in the Face of Trauma* session content. For aim 3, the pilot trial will enroll an analytic sample of 60 New Orleans people living with HIV individually randomized to parallel NOLA GEM (intervention) or GEMA-alone (control) arms at a 1:1 allocation for a 21-day period. Acceptability and feasibility will be assessed via enrollment, attrition, active daily use through paradata metrics, and prevalidated usability measures. At the postassessment time point, primary end points will be assessed via a range of well-validated, domain-specific scales. Care engagement and viral suppression will be assessed via past missed appointments and self-reported viral load at 30 and 90 days, respectively, and through well-demonstrated adherence self-efficacy measures.

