### Study Objectives

This study aims to develop, pilot, and refine *NOLA GEM*, a smartphone-delivered LIFT adaptation informed by within-person geographic ecological momentary assessment (GEMA) data on time-variant stressors and symptom profiles among violence-affected people living with HIV in New Orleans [49]. Mobile health (mHealth) and internet-delivered interventions that activate evidence-based, trauma-informed psychotherapies have shown promise in enacting clinically significant PTSD improvement [50,51], with a 2018 Cochrane review pointing toward opportunities to bolster the evidence base and calling for closer attention to mechanisms of change [52]. The benefits of mHealth in advancing CoC milestones are well established [53,54], although innovations in cultural and contextual tailoring are urgently needed to ensure sustainability [55-57]. These benefits can be augmented by in-app geospatial awareness, building on prior work that leverages GPS to (for example) alert mHealth users to the proximity of HIV and sexual and reproductive health clinics [58,59] or, in contrast, use real-time GPS coordinates to (1) describe routine activity paths and (2) apply this geospatial awareness at a hyperlocal level to address the potential of spatial-environmental stressors to evoke traumatic stress and drive CoC churn and, alternatively, identify restorative spaces to reduce stress. By developing NOLA GEM, we engage these opportunities to advance the field; meet the needs of New Orleans people living with HIV [41,45,46]; and address the nonlinear, holistic nature of traumatic stress [1,2,4,8] by delivering effective coping skills education and reinforcement in real time [33].

We will engage these objectives via the following specific aims:

*Aim 1*: conduct GEMA with violence-affected people living with HIV to (1) describe activity spaces associated with CoC and (2) assess potential mediated pathways through mood, mental health, substance use, trauma cognitions, and coping to inform novel intervention targets.*Aim 2*: develop NOLA GEM, an mHealth LIFT adaptation, incorporating GEMA-informed mediators of well-being tailored for New Orleans people living with HIV.*Aim 3*: test the feasibility, acceptability, and preliminary efficacy of the NOLA GEM app against GEMA alone on primary CoC (care engagement, ART adherence, and viral suppression) and secondary mental well-being end points.

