### Aim 3: Acceptability, Feasibility, and Preliminary Efficacy

#### Trial Design

The pilot trial will be a single-blind parallel superiority trial assessing NOLA GEM (treatment arm) against GEMA alone (control arm) for a period of 21 days, allocated at a 1:1 ratio. In contrast to aim 1, the NOLA GEM app is capable of delivering SMS text message–linked daily diaries and recording GPS coordinates without recourse to third-party software. The GEMA-alone control was chosen to control for any intervention effects of recording daily mood, experiences, and other psychosocial variables as some research has demonstrated improvements in outcomes such as PTSD, depressive symptoms, and emotional awareness in participants recording their experiences using EMA methods [112-115] (aim-2 interviewees, unprompted, disclosed similar enhancements in self-awareness during their experience as aim-1 participants). This design establishes a high-resolution comparator to NOLA GEM, capturing GEMA data across both trial arms while potentially isolating the effects of JITAI-based momentary provision of LIFT content as a hypothesized mechanism of action.

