#### Participants and Procedures

With eligibility determined, participants will be randomized, and a baseline appointment will be scheduled. Quota sampling will ensure a ≥50% female, 50% aged >40 years and 50% aged <40 years, and ≥75% Black sample, reflecting the unique drivers and PTSD symptom constellations endured by women and Black Americans while also reflecting New Orleans people living with HIV demographics.

At baseline, informed consent will be obtained, and an in-person or Zoom assessment will be administered by the research staff. The NOLA GEM app (through which participants can be assigned to either treatment or control user types via an integrated back end) will be installed on participants’ smartphones from the Crowdbotics-hosted Apple App Store or Google Play Store, and a detailed onboarding will be conducted by research staff to ensure uniform comprehension of the app’s features, the nature of GEMA, and the wording of daily diary items. Although participants will be instructed on the expectations, functional affordances, and user expectations specific to their trial arm, they will be blinded to their explicit treatment versus control assignment.

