### Primary Outcomes

Primary, distal outcome measures will be assessed at the immediate postintervention time point (within 1 week of completing the 21-day intervention period) and the 30- and 90-day follow-up assessments, as specified in the following sections.

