#### CoC Milestones

Primary outcomes, representing recognized HIV CoC milestones [1,21,23], will be operationalized as follows via a postassessment survey.

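### Viral suppression, a primary outcome, is the self-reported latest test with no condition on the test date, so a result from before randomisation can count as a post-intervention outcome

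*Protocol article*

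**What the plan says.** Aim 3 in the Study Objectives lists the end points as "primary CoC (care engagement, ART adherence, and viral suppression) and secondary mental well-being end points", and the CoC Milestones section confirms the status: "Primary outcomes, representing recognized HIV CoC milestones". The Viral Suppression section then defines the measure as a self-report item "asking participants whether their most recent HIV viral load test result was <50 copies/mL at the 90-day follow-up assessment". The abstract describes it as "self-reported viral load at 30 and 90 days, respectively", where the 90 days belongs to viral load, and adds no condition on the test.

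The intervention runs "for a period of 21 days, allocated at a 1:1 ratio". Primary outcomes are assessed just after the intervention "and the 30- and 90-day follow-up assessments, as specified in the following sections". That sentence does not say whether day 90 counts from baseline or from the end of the 21 days. Several secondary outcomes are placed at 30 days after baseline, which hints at a baseline origin, but nothing says so for day 90.

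On the order of events, Participants and Procedures under Aim 3 says: "With eligibility determined, participants will be randomized, and a baseline appointment will be scheduled". Randomisation therefore precedes baseline by an unstated gap.

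Study Settings places everything after intake on the app or the phone. No Aim 3 section describes a study viral load, collection of the test date, or a check against medical records. The two neighbouring primary measures do carry a look-back window: 90 days for missed appointments and 30 days for the adherence visual analogue scale.

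**The concern.** The item asks for the latest result whenever it was taken. A participant last tested before randomisation supplies a pre-treatment value that is then analysed as a post-treatment primary outcome. Randomisation makes such values equal between arms in expectation, so they dilute any real difference.

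Two further effects follow. Care engagement is itself a target of the intervention, so the chance of having a new test may differ by arm, and the direction of the resulting distortion cannot be predicted. Also, a participant who has left care can go on reporting an old suppressed result, which hides the failure this milestone should detect.

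This is more than analysis detail that a protocol article leaves to another document. It concerns which data are collected: if the date is never asked, no later analysis can separate results from before and after randomisation. The Results section says the pilot will be used to discard components that look ineffective and to support an application for a full trial, so an avoidable pull toward no difference matters even without a formal test.

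**Working it through.** The documents state no suppression rate, testing interval or power for this outcome, so there is no figure of theirs to reproduce. The check asks what share of latest tests could predate baseline.

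**Inputs from the protocol:** intervention length 21 days; follow-up at day 90, origin not stated; analytic sample 60 (30 per arm).

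**Assumed inputs:** interval T between routine tests of 90, 120, 180 or 365 days; window W from baseline to assessment of 90 days, or 90 + 21 = 111 days if day 90 counts from the end of the intervention.

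**Formulas for the share predating baseline**
- Regular testing at random phase: max(0, 1 − W/T).
- Irregular (Poisson) testing with mean interval T: exp(−W/T).

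| T (days) | W = 90, regular | W = 90, irregular | W = 111, regular | W = 111, irregular |
|---|---|---|---|---|
| 90 | 0% | 37% | 0% | 29% |
| 120 | 1 − 90/120 = 25% | 47% | 1 − 111/120 = 8% | 40% |
| 180 | 1 − 90/180 = 50% | 61% | 1 − 111/180 = 38% | 54% |
| 365 | 1 − 90/365 = 75% | 78% | 1 − 111/365 = 70% | 74% |

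In a sample of 60 with regular testing at T = 180, this is 60 × 0.50 = 30 people for W = 90 and 60 × 0.383 = 23 for W = 111.

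**Correction for the time of randomisation.** The shares above are before baseline. With a gap of g days from randomisation to baseline, the share before randomisation under regular testing is max(0, 1 − (W + g)/T). Each day of gap lowers it by 1/T: 0.8 percentage points at T = 120, 0.6 at T = 180 and 0.3 at T = 365. The gap is not given, so the table is an upper bound for the pre-randomisation share under each assumption.

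**Dilution.** If a fraction f of results predates randomisation equally in both arms, a true difference d appears as d × (1 − f). As an illustration, take assumed true rates of 70% and 90% (d = 20 points), old results suppressed at 70% in both arms, 30 per arm and two-sided alpha 0.05.

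| f | Observable difference | Power |
|---|---|---|
| 0% | 20 points | 49% |
| 25% | 15 points | 28% |
| 50% | 10 points | 14% |
| 75% | 5 points | 6% |

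The 70% and 90% are not from the documents. They only show how the loss scales.

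**The case against.** **The size is not documented.** A reader might infer that many results will predate randomisation. The protocol does not support that: the assumed range starts at 0%, and with regular testing at least every 90 days the problem nearly vanishes. Aim 3 takes over the earlier aims' inclusion criteria, which drew on people in HIV specialty care, and the missed-appointments item presumes visits within 90 days. Neither point establishes a testing interval, and Aim 3 also recruits in the community, so frequent testing cannot be assumed either. This objection stands against any fixed figure, but not against the defect.

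**The pilot does not rest on this outcome.** Limitations says the trial is underpowered for efficacy by design, and no sample size or go/no-go threshold depends on viral suppression. Even undiluted, the illustration gives only 49% power. Dilution by old results pulls toward no difference and so would not by itself create a false signal. This stands, and it lowers the severity.

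**Tests during the 21 days are legitimate.** One might also count tests taken before day 21 as uninformative. They follow randomisation and occur under treatment, so they do not belong to this complaint.

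**Restricting to new tests has its own bias.** The obvious repair is to count only participants with a post-randomisation test. Whether such a test exists may be affected by the intervention, so the restriction replaces dilution with selection. At T = 180 and W = 90 it would also drop about 30 of 60 people. This stands, and it shapes the fix.

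**The full item is not shown.** It is adapted from a cited source, and the questionnaire might ask for a date. That is possible, but the protocol states windows for the neighbouring items and none here.

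**Conclusion.** The point holds at moderate severity. As defined, a primary outcome admits results from before randomisation, and nothing in the protocol would allow them to be identified later. Those results cannot reflect the intervention and shrink the observed difference in proportion to their share.

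That share is unknown. Under regular testing it ranges from 0% to 75% before baseline if day 90 counts from baseline, and from 0% to 70% if it counts from the end of the intervention. It is somewhat lower before randomisation and higher if testing is irregular. All of this rests on assumed intervals of 90 to 365 days.

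A reader might conclude that the outcome is worthless or that the trial cannot proceed without the change. The documents do not support either: tests after randomisation remain informative, and the trial makes no formal efficacy claim.

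**What to change.** 1. Ask the month or date of the most recent viral load test together with its result, at baseline and at day 90. State whether day 90 counts from baseline or from the end of the 21 days.
2. Keep all randomised participants in the main comparison, with baseline suppression as a covariate. This comparison stays diluted, but the next item shows by how much.
3. Report by arm the proportion with a test dated after randomisation.
4. Present suppression among those with such a test as a supporting analysis, labelled as open to selection.
5. Add a sensitivity analysis that counts the absence of a post-randomisation test as not suppressed.

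The cost is one extra survey item at two assessments. The supporting analysis will have fewer participants: with regular testing every 180 days and 90 days from baseline, about half would have no test since baseline. Recalled dates will be approximate, but month-level recall is enough to place most tests before or after randomisation.

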### Secondary Outcomes

#### Mental Well-Being

Diverse domains of psychosocial and emotional well-being will be assessed among all aim-3 participants.

##### PTSD Assessment

At 30 days after baseline, the *PTSD Checklist for DSM-5*, a 20-item self-report measure that assesses the presence and acuity of *DSM-5* PTSD symptoms, will assess traumatic stress burden for participants [123]. Considered an acceptable means of provisional diagnosis, the PTSD Checklist for DSM-5 has demonstrated psychometric soundness and acceptable continuity between Diagnostic and Statistical Manual of Mental Disorders, Fourth Edition, and *DSM-5* PTSD conceptualizations [124]. In addition, a range of daily diary measures (detailed in Multimedia Appendix 3) will record daily fluctuations in posttraumatic stress symptom acuity.

##### Anxiety and Depression

At 30 days after baseline, the 14-item *Hospital Anxiety and Depression Scale* will assess the presence and severity of anxiety and depression symptoms. Fielded and assessed for decades [125], the Hospital Anxiety and Depression Scale is shown to possess acceptable construct validity and internal consistency among clinical samples [126]. In addition, a mood checklist is administered via the daily diaries prompting participants to mark all moods they have experienced in the interim since their last daily diary (eg, “excited,” “relaxed,” or “scared”; Multimedia Appendix 3).

##### Effective Coping

At 30 days after baseline, the Brief *Coping Orientation to Problems Experienced* and *Coping Self-Efficacy Scale* will measure participants’ recourse to adaptive versus maladaptive styles of coping [127]. Translated into French, Spanish, Malay, and Russian and fielded successfully among broadly heterogeneous populations, the Brief Coping Orientation to Problems Experienced consistently evidences acceptable psychometric properties, although its internal factor structure remains contested [128]. The Coping Self-Efficacy Scale also demonstrates good reliability and validity, including among samples of in-care people living with HIV [129]. Via a checklist, coping strategies (“getting emotional support from others” and “criticizing myself”) will be logged in the aim-3 daily diaries (Multimedia Appendix 3).

##### Hazardous Substance Use

At 30 days after baseline, the 3-item *Alcohol Use Disorders Identification Test*, a valid instrument for detecting heavy, potentially unhealthy alcohol use patterns [130], will be applied to that end in aim 3. The “Alcohol/Drugs” section of the widely used *Addiction Severity Index* will assess the effects of participants’ alcohol and drug use across key domains of daily functioning [131]. Dedicated daily diary items will also prompt participants to describe patterns of alcohol and drug use since “last night” (morning daily diary) or “your last daily diary” (afternoon daily diary; Multimedia Appendix 3).

##### Domain–General Stress

Finally, at 30 days after baseline, the *Perceived Stress Scale–4* will measure situational subjective stress among aim-3 participants [132]. In addition, a 24-item aim 1–generated novel daily stressor severity checklist operationalizing a wide array of potential sources of stress arousal (eg, community and police violence, intrafamilial strife, and employment challenges) will assess multidomain stress experienced by aim-3 participants at the 30-day follow-up relative to their baseline stress burden.

#### Analytic Approach

Consistent with aim 1, aim-3 data will be cleaned and saved in SAS data files (SAS Institute), with extensive consistency checks conducted at all levels of data [66]. At the completion of each check, the data will be added to the existing database for analysis. GPS data will be stored on a password-protected server and constructed into activity paths, replicating the aim-1 approach [66].

Preliminarily, descriptive and crude bivariate associations between variables of interest will be generated. Daily diary completion rates and agreement with aggregate retrospective survey data for comparable measures will be calculated. Data reduction techniques, mitigating the high volume and dimensionality of GEMA-derived data, will include the creation of composite indexes of cumulative risk, with exploratory factor analysis, assessment of internal consistency, and Bonferroni correction applied as warranted.

Aim-3 analyses of preliminary efficacy will include analysis of each day-to-day distal outcome as a continuous variable as well as average exposures across the total intervention period. We will explore potential transformations to approach normality on key response variables [133]. Linear mixed-effects models will relate day-level outcomes to day-level indexes of cumulative risk and protective exposure derived originally from aim 1, adjusted for baseline values [134]. Random effects will be included to account for within-subject series correlations. Control variables will be modeled as fixed effects.

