#### Sample Size Considerations

The target sample size is approximately 100, which will accommodate an anticipated ≥10% attrition rate based on previous experience enrolling local violence-affected in-care people living with HIV, for an optimal analytic sample of 60 (30 per arm).

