### Limitations

As a small-scale pilot trial, aim 3 is subject to a number of inherent limitations. First, and by design [142], it is underpowered to examine efficacy in a formal hypothesis-driven manner. Mediation analyses of proximal outcomes will necessarily be exploratory in nature and inform the causal pathway hypotheses for the planned RCT. Although the selection of control conditions for mHealth trials remains an area of active investigation and debate [143], a passive GEMA-alone control may inflate preliminary estimates of NOLA GEM (incorporating GEMA+LIFT coping skills) efficacy on primary outcomes, an issue that is potentially exacerbated by the small sample size [144]. Adaptations of complex, sequential, and multicomponent group interventions risk dismantling key mechanisms of action that undergird effectiveness in their original contexts [33,34,101]. Adaptation to mHealth across HIV science remains a highly active but often methodologically impromptu area [145]. Pragmatic considerations required us to deprecate certain components of LIFT as originally manualized [33] and demonstrated to reduce traumatic stress [34,36]. Group cohesion and dedicated in-person facilitation of the group member disclosure and support processes define the LIFT intervention trajectory, which is sequenced across 15 sessions [33]. We abstracted the CTSC-based strategies built into NOLA GEM from their original, in-person, session-by-session framework to activate the “just-in-time” aspect of a JITAI adaptation while mitigating ethical concerns that, if faced with an acute stressor, a NOLA GEM user would be denied the best-suited coping support if they had not yet reached the appropriate session had a strictly linear intervention model been retained. Similarly, although a peer-to-peer support forum or social media–style feature [146,147] in which users could interact pseudonymously was briefly considered, lacking active human (vs algorithmic) content moderation, such a space could become consumed with off-topic, inane, or even outrage-inducing user-generated content and external media [86,148]. In addition, by recruiting people living with HIV who were either violence-affected individually or lived in a high-violence neighborhood, a degree of heterogeneity in needs was introduced into the aim-1 and aim-2 samples, which may have swayed the formative insights—and, by extension, intervention design—derived from the *New Orleans Alcohol Use in HIV* study subsamples. Although violence exposure at the within-person and neighborhood levels is associated with distinct sequelae among people living with HIV, it is our intention that the multitude of possible NOLA GEM user journeys can offer the necessary support to a wide range of personal violence histories. By nature, an acceptability and feasibility trial will provide insights on many of these concerns, whereas merged paradata and GEMA data will permit high-resolution analyses of users’ engagement with and navigation of NOLA GEM [149].

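### Where a family of tests is corrected, Holm's step-down would serve at least as well as the single-step Bonferroni the plan names; the gain is small and conditional

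*Protocol article*

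**What the plan says.** The second paragraph of Analytic Approach (protocol article) covers preliminary work: descriptive statistics, crude bivariate associations, diary completion rates and data reduction. Its last sentence begins "Data reduction techniques, mitigating the high volume and dimensionality of GEMA-derived data, will include the creation of composite indexes of cumulative risk" and goes on to exploratory factor analysis, a check of internal consistency, and "Bonferroni correction applied as warranted". No other multiplicity method is named in the article.

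The efficacy analysis is in the next paragraph: "Linear mixed-effects models will relate day-level outcomes to day-level indexes of cumulative risk and protective exposure derived originally from aim 1", adjusted for baseline values. That paragraph states no multiplicity rule. No test family, alpha level or number of tests is defined in the article.

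Under Limitations the authors say of the pilot that, by design, "it is underpowered to examine efficacy in a formal hypothesis-driven manner". Sample Size Considerations gives an analytic sample of 60, or 30 per arm.

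**The concern.** Bonferroni compares every p value with alpha/m. Holm's procedure uses that threshold only for the smallest p value and relaxes it after each rejection, and it protects the family-wise error rate to the same degree. Naming the single-step version therefore accepts some avoidable loss of power in whichever family is corrected. In a pilot that is already short of power, and whose Results section says its findings will be used to trim components before a full trial, a free gain in sensitivity is worth having. What is at stake is modest: some secondary rejections within a corrected family. The validity of the analysis is not in question.

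**Working it through.** **No plan figure to reproduce.** The article states no alpha, power, effect size or number of tests, so the loss in this trial cannot be computed from it. The figures below are illustrations under assumptions.

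**Why Holm never rejects less.** Order the p values p(1) ≤ … ≤ p(m).
- Bonferroni rejects every p ≤ 0.05/m.
- Holm compares p(i) with 0.05/(m − i + 1), in order, and stops at the first failure.
- For m = 3 the Holm thresholds are 0.0167, 0.025 and 0.05. Bonferroni uses 0.0167 for all three.
- The first thresholds are equal and the later Holm thresholds are larger, so every Bonferroni rejection is also a Holm rejection. Because the first thresholds are equal, the probability of at least one rejection is identical.

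**Inputs.**
- From the article: 30 per arm (Sample Size Considerations), and three continuum-of-care domains (Study Objectives) as one plausible family size.
- Assumed: family-wise alpha 0.05 two-sided; m = 3, with m = 10 as a larger case; effects d of 0.3, 0.5 and 0.8 SD; equicorrelated normal test statistics with correlation 0 to 0.5.

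**Bonferroni power per test.** In the normal approximation this is about Φ(d√(30/2) − z), where z is the two-sided critical value at 0.05/m.
- d = 0.5 gives d√15 = 1.936.
- m = 3: z = 2.394, so Φ(−0.458) ≈ 32.4%.
- m = 10: z = 2.807, so Φ(−0.871) ≈ 19.2%.

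**Bonferroni against Holm, by simulation (200,000 replicates).** Average power per test when all effects are real; ranges run over correlation 0 to 0.5:

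| m | d | Bonferroni | Holm | Gain (points) |
|---|---|---|---|---|
| 3 | 0.3 | about 11% | 11.7–12.8% | 0.8–1.8 |
| 3 | 0.5 | about 32% | 37.0–37.9% | 4.6–5.5 |
| 3 | 0.8 | about 76% | 82.9–84.6% | 7.0–8.6 |
| 10 | 0.3 | about 5% | 5.2–5.9% | 0.2–0.9 |
| 10 | 0.5 | about 19% | 21.3–23.7% | 2.1–4.6 |
| 10 | 0.8 | about 61% | 73.0–75.5% | 11.6–14.0 |

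**When only one effect is real (d = 0.5).** With m = 3 the gain is at most about 0.2 points (for example 32.3% to 32.5%). With m = 10 it is at most about 0.05 points.

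**At least one rejection.** Identical for the two methods in every setting. For m = 3, all d = 0.5 and correlation 0, both give 69.0%.

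**Error control.** Holm's simulated family-wise error stayed at or below 5% throughout; the largest value was 4.96%, with three independent nulls.

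**Underpowering remains.** One unadjusted two-sided 0.05 test with 30 per arm has 21% power at d = 0.3 and 49% at d = 0.5. No choice of correction can lift a single test above those figures.

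**The case against.** The strongest reply is that Bonferroni is not stated as the correction for the trial's efficacy comparisons. It is conditional and sits with factor analysis and internal consistency in a data-reduction sentence, while the efficacy paragraph carries no multiplicity rule. That reading is right, and it limits the point in three ways.

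- A reader might infer that power on the PTSD, anxiety, depression, coping and stress scales is being given away. The article does not say that those comparisons will be corrected, so no efficacy power loss is established. A calculation that treats 13 outcomes as one corrected family describes a procedure the article does not state. Its largest Holm gain, 43% to 53% at 0.7 SD and correlation 0.5, also needs all 13 outcomes to move.
- A reader might infer that real signals will be dropped before the full trial. The Results section speaks of trimming underused or seemingly ineffective adaptive components. Nothing makes adjusted significance the rule for that decision.
- A reader might call the loss entirely free to avoid. It is not quite: Bonferroni has simple matching simultaneous confidence intervals and Holm does not, and intervals matter in a pilot that disclaims formal testing.

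It can also be said that Bonferroni is valid and that the families may be defined in an unshown analysis plan. Both are true. But the point does not rest on missing detail. The article names a method, and a uniformly at-least-as-powerful test with the same error guarantee and no added assumptions is available for whichever family the authors had in mind.

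**Conclusion.** The point holds as a minor improvement. Single-step Bonferroni is the only correction named, and for any family that is corrected Holm gives the same protection and never rejects less. Under the assumptions above, the gain in average power per real effect is about 0 to 9 points with 3 tests and about 0 to 14 with 10. The top of each range needs every effect in the family to be real and large. The article does not support a claim that the trial's efficacy analysis loses power through this sentence, nor that Holm would change the declared status of the pilot as underpowered.

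**What to change.** In Analytic Approach, replace *Bonferroni correction* with *Holm step-down correction* for any family of tests that is corrected. Report unadjusted 95% confidence intervals beside the Holm-adjusted p values and label them as unadjusted.

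The cost is a short wording change and a standard software option; no new data or design change is needed. The one real drawback is the lack of simple matching simultaneous intervals, which the unadjusted intervals make visible but do not remove. The change does not settle whether the between-arm comparisons are to be corrected; the article leaves that open.
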